### Interventions

This study will compare two conditions: the JP intervention and psycho-educational parent counselling as a control group. Parent counselling, a widely accepted and commonly implemented practice shown to be beneficial for parents of children with ID [53], was selected as the control group for ethical reasons, to ensure participants receive meaningful support during their participation in the study. It is important to note the differences between these conditions: Psycho-educational parent counselling primarily addresses mothers’ experiences of parenting a child with ID, providing guidance, support, and coping strategies. In contrast, the JP intervention specifically targets mother-child play interactions. This difference will also affect how the interventions will be delivered: the JP intervention will involve dyadic play with the mother, child, and therapist in the family’s natural home environment, while the psycho-educational parent counseling will involve the mother only and will be conducted online as a preferred method for parent counseling.

### JP dyadic CAT-based intervention

The JP intervention has been developed specifically for this study by the authors of this article, who are trained and experienced creative arts therapists from the fields of music, drama, and visual arts therapies. The JP intervention focuses specifically on the early stages of play: sensorimotor play and object play as these are especially relevant for young children with developmental delays and ID. Given the intervention’s goal of improving the quality of mother-child interactions, sensorimotor and object play offer dyads play activities suited to the child’s developmental level and offering them opportunities for mutual engagement and enjoyment. By joining the child through familiar play activities, therapist and mother empower the child to lead the interaction, increasing their initiation, motivation, and cooperation. As the intervention progresses, the dyad may even venture into new and more advanced forms of play, such as pretend and social play. The JP intervention aims to enhance the mother-child relationship and improve the child’s socioemotional development. The intervention will include eight weekly 45-minute dyadic play sessions with the child, mother, and a music or drama therapist in their home environment. The number of sessions was selected to be eight, since it is considered a minimum ‘dosage’ for CAT-based family therapy [19]. The intervention will employ and foster musicality, movement, action, and emotional expression, reflecting the cross-modal nature of children’s play. The intervention protocol will provide instructions for maintaining intervention fidelity, while allowing flexibility to tailor the meetings to each dyad’s strengths and needs.

The intervention’s objectives are to: 1. Encourage mothers and children to adopt a playful approach that fosters flexibility, creativity, imagination, and mutual enjoyment. 2. Support and scaffold developmentally appropriate dyadic play interactions based on the child’s level and preferences. 3. Promote children’s initiation and leading mutual play interactions while enhancing their cooperation skills. 4. Promote sensitive and responsive parental behaviors during play interactions.

The intervention protocol presents a variety of games and ideas according to the different developmental stages of play: sensorimotor play, object play, and pretend play. The therapist will identify existing forms of play and participate in mutual play interactions, while suggesting and introducing novel ideas and games that the dyad may choose to join. The therapist’s role as an active player allows them to model playfulness for the child and mother while expanding and developing their play. Play interactions will be advanced by following the child’s lead, humor, improvisation, repetition, turn-taking, and exchanging roles. A pilot study was conducted involving six meetings with a mother-child dyad in order to evaluate and refine the intervention protocol. The JP intervention model is depicted in Fig 3. The intervention meetings will be video-recorded for the purpose of supervision, intervention fidelity, and research.

**Fig 3 pone.0349576.g003:**
[figure not shown]
JP Intervention Model.

### Psycho-educational parent counseling

The control arm of the psycho-educational parent counseling intervention will consist of eight weekly 45-minute sessions conducted online via Zoom, involving the mother and a trained parent counselor. The sessions will follow the Adlerian model, a well-known and contemporary psycho-educational parent counseling approach supported by ongoing professional training programs [53]. The parent counseling intervention will specifically address key issues and concerns associated with parenting a child with ID such as understanding their developmental needs and challenges. The intervention will provide instructions for maintaining intervention fidelity, while allowing flexibility to tailor the meetings to each mother’s strengths and needs in parenting their child with ID.

The parent counseling intervention’s objectives are: 1. To promote a positive parenting style, by encouragement of the child in order to foster their sense of significance and belonging within their family and the broader social context, as key factors to the children’s healthy development. 2. To identify and address maladaptive behaviors in the parent-child relationship, e.g., the parent overprotecting their child with ID, managing challenging child behaviors, or promoting the child’s acquisition of new skills. 3. To address maternal stress and family dynamics, e.g., difficulties that may arise between parents, or among siblings of the child with ID [54]. Parent counselors will collaborate with each mother to establish individualized goals to work on during the intervention according to the mother’s needs and desires.

### Training interventionists

In the JP intervention condition, music and drama therapists with M.A. certification and previous experience working with children with ID will undergo a three-hour training session on the intervention protocol and will participate in bi-weekly supervision sessions to support their work and ensure treatment fidelity. In the control condition, certified Adlerian parent counsellors will undergo a three-hour training session on counselling parents of children with ID and will participate in bi-weekly supervision sessions by an experienced parent counsellor to support their work and ensure treatment fidelity.

### Assessment of treatment fidelity

To ensure the interventions are delivered as intended by protocol [55], therapists and parent counselors will fill out an implementation checklist after each session and document significant events from the intervention meetings. All dyadic play sessions will be video-recorded to ensure fidelity of the intervention and accurate interpretation of treatment effects [56]. Supervision will be provided by trained and experienced supervisors to maintain method compliance and competence.

## Measures

### Descriptive measures

A demographic questionnaire will be used to collect background information about the parents’ age, ethnicity, education, profession, and income, as well as the participating child’s age, diagnosis and treatment, along with additional questions about family members and living situation.Vineland Adaptive Behavior Scales-3 parent/caregiver comprehensive form (VABS-3) [57] assesses the child’s developmental and adaptive behavior abilities in three core domains: communication, daily living skills, and socialization. The form consists of 381 items scored on a 3-point Likert-type scale ranging from 0 to 2. A higher score on the form indicates higher developmental and adaptive behavior abilities. The VABS-3 comprehensive form will be administered to the child’s mother, as it is commonly used to support the diagnosis of intellectual and developmental disabilities. The comprehensive level form, when used with children under the age of seven, has been shown to have excellent internal consistency (Cronbach’s α = .99), excellent test-retest reliability of .85, and excellent inter-rater reliability of .86 [57].

### Outcome measures regarding quality of parent-child interaction

#### Primary outcome measure.

Emotional Availability Scales (EAS) [58] assesses the quality of the parent-child interaction. The coding system is a standardized observational video analysis tool evaluating four dimensions related to parental behaviors: sensitivity, structuring, non-intrusiveness, and non-hostility, and two related to the child’s behaviors: responsiveness and involvement. Each dimension is coded on a variety of items scored on a 7-point Likert-type scale with a higher score signifying higher emotional availability. The total sum scores will be calculated for the results. The EAS will be coded based on a 7-minute recording of an episode of social play without toys. The ICC inter-rater reliability has been reported in previous studies to be between .76−.96 [24]. The EAS have been validated for construct in a large number of studies as well as being used in studies with children with ID [21,59] according to the adapted guidelines issued by the EAS authors [60].

#### Secondary outcome measure.

Parent-Child Interpersonal Synchrony (IPS) will be evaluated by micro-analyzing the movement coordination between the parent and child while moving together to an original musical piece (approximately 3 minutes long) during the two assessment meetings. IPS will be measured using OpenPose, a multi-person 2D pose estimator, to extract skeletal information from the videos. The positions of the mother and child during the mutual movement task will be examined for coherence and variance using the cross-wavelet analysis method, forming an index between 0 and 1 of the degree of interpersonal synchrony between mother and child, with a higher score signifying an optimal outcome of higher interpersonal synchrony, as described in Grinspun et al. [61].

### Mediation measures

Parental Playfulness Scale (PPS) [62] evaluates the parent’s playfulness. The PPS is a standardized observational video analysis tool that assesses parental creativity, imagination, humor, pretend play, and curiosity while playing with their children. The PPS is composed of three subscales: parent’s playfulness, following the child’s lead, and peer-like behavior rated on a 7-point Likert-type scale from 1 to 7, with a higher score signifying more playfulness. All scores are averaged into a single playfulness score for each parent. The PPS will be scored based on the video-recorded episodes of free play and play with a doll. The PPS has been shown to have high interrater reliability of 0.8 [38,63] and has been used to assess the playfulness of parents to children with ID [27].Test of Playfulness (ToP; version 4.2) [64] evaluates the child’s playfulness. The ToP is a standardized observational video analysis tool comprised of 30 items rated on a 4-point Likert-type scale from 0 to 3, evaluating the extent, intensity, and skill of the child at play, with a higher score signifying more playfulness. All scores are averaged into a single playfulness score for each child. The ToP will be scored based on the video-recorded episodes of free play and play with a doll. Studies have established the reliability and validity of the ToP determining goodness-of-fit according to the Rasch analysis model when used with children with ID [35,36], and has been used in previous intervention studies [37].

The outcome measures of EA, child playfulness (ToP), and parent playfulness (PPS) will be coded by blind and trained researchers. Interrater reliability will be determined by comparing 20% of the data to an additional blind and trained scorer using the interclass correlation coefficient [65] to establish consistency of independent ratings.

### Data management and storage

Data will be securely stored on an organizational Google Drive account, ensuring the privacy and anonymity of participants. Participants will be identified by code numbers in video recordings and interview data. Personal data will be stored separately with password-protected access. The data will be retained for research purposes for four years and then destroyed.

## Data analyses

### Quantitative data

Univariate statistical analysis will be used to compare demographic and baseline variables between condition groups. To assess the effects of the interventions, a Linear Mixed-Effects Model (LMM) using a Restricted Maximum Likelihood (REML) approach, including time (pre vs. post), group (JP intervention vs. control), and their interaction, will be used. The covariates of the child’s gender and the VABS-3 score will be adjusted based on both clinical and statistical relevance. To assess associations between EA and IPS to parent and child playfulness scores, Spearman’s correlation coefficients will be calculated. To examine whether the playfulness scores of parents and children (each score entered separately) mediate the relationship between the intervention and the change scores of the primary outcome of EA total sum scores and IPS, Hayes’s [66] PROCESS macro will be used, selecting model 4, 5, 7, or 14 based on the relationship between the covariates involved and the study variables. We acknowledge that, using multiple regression with three to four predictors (the treatment group, parents’/child’s playfulness score, children’s VABS-3 score, and gender), and considering an alpha level of .05, a power of .80, and an effect size of f² = .02, a sample size of 59–65 participants is required (see Daniel Soper’s calculator for a priori sample size [67]). Consequently, given our modest sample size of n = 60, the proposed mediation analyses should be regarded as exploratory and interpreted with caution. Moreover, to minimize the risk of overfitting, only covariates with both theoretical and statistical justification (e.g., child’s VABS-3 score, gender) will be incorporated into the model, and indirect effects will be estimated via bootstrap confidence intervals.

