### Sample size

Previous studies using pre/post EA total sum scores to compare the effectiveness of parent-child interventions [47,48] have reported medium to very large (0.5–1.17) effect size according to Cohen’s [49] criteria. The study is powered to detect a large between-group effect size of Cohen’s d = 0.8 in the primary outcome of change in EA total sum scores between baseline and post-intervention. With a significance criterion of α = 0.05 and power = 80%, the minimum sample size is n = 52 with n = 26 in each sample. Assuming drop-out does not exceed 10%, the aim is to recruit 60 families in total. Furthermore, given the nature of the study involving a short-term home-delivered intervention, n = 30 families in the JP intervention group seems to be a feasible yet significant number.

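### The primary pre/post mixed model is valid but estimates the raw difference in mean EA change: baseline EA is not used as a covariate, and gender and VABS-3 as main effects add essentially no precision

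*Protocol article*

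**What the plan says.** The Sample size section powers the trial on the "primary outcome of change in EA total sum scores between baseline and post-intervention". It states that "The study is powered to detect a large between-group effect size of Cohen’s d = 0.8", gives 26 dyads per arm as the minimum, and allows 10% dropout within a target of 60 families.

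The Quantitative data section names a REML linear mixed model "including time (pre vs. post), group (JP intervention vs. control), and their interaction, will be used". Child gender and the VABS-3 score "will be adjusted based on both clinical and statistical relevance". The only interaction named is time by group. Baseline EA enters as one of the two outcome rows per dyad and is not listed as a covariate.

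The Study design section gives two quantitative assessments, before the programme and one week after it. The Study procedures section places the baseline assessment after randomization, in mothers who know their condition.

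**The concern.** With two measurements per dyad and a separate baseline mean for each arm, the time-by-group coefficient is the difference between arms in mean change. Two consequences follow.

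- **The adjustment is close to inert.** A covariate that is constant within a dyad and enters only as a main effect shifts the pre and post values equally, so it cancels from the change. A reader who sees gender and VABS-3 in the model would expect some gain in precision and would get essentially none.
- **Available precision is left unused.** Subtracting baseline EA fixes its coefficient at 1. Estimating that coefficient, as ANCOVA does, gives a residual variance that is no larger and is usually smaller. This matters in a trial sized for d = 0.8 when the article's own cited range starts at 0.5.

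A smaller issue is the inclusion rule. Making covariate entry depend partly on statistical relevance leaves the form of the primary model open to the data.

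**Working it through.** **1. Inputs.** From Sample size: d = 0.8 on EA change, alpha 0.05, power 80%, 26 per arm, dropout up to 10%. From Study procedures: 1:1 allocation. From Study design: two time points. From Quantitative data: the model terms. Assumed, because the article does not give them: the pre-post correlation rho of EA, and equal pre and post SDs (σ).

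**2. The plan's own figure.** Two-sample t test, two-sided, noncentrality d·√(n/2), df = 2n − 2.
- n = 25 per arm: power 79.2%.
- n = 26 per arm: 0.8·√13 = 2.88, df 50, power 80.7%.

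The stated minimum of 26 per arm is reproduced. Dropout: 52/0.90 = 57.8, so 58, which the target of 60 covers.

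**3. Does the model equal the change-score comparison?** Three simulated complete data sets, 30 per arm, time-by-group estimate (SE):

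| Set | LMM without covariates | LMM + gender + VABS-3 (main effects) | Change-score comparison | ANCOVA on baseline only, SE |
|---|---|---|---|---|
| 1 | 0.7246 (0.283) | 0.7246 (0.283) | 0.7246 (0.283) | 0.243 |
| 2 | 0.2344 (0.296) | 0.2344 (0.296) | 0.2344 (0.296) | 0.277 |
| 3 | 1.3253 (0.291) | 1.3253 (0.291) | 1.3253 (0.291) | 0.264 |

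The first three analyses agree. ANCOVA has the smaller SE each time. With gender and VABS-3 added to the ANCOVA, its SEs fall further, to 0.220, 0.271 and 0.246.

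**4. With dropout.** With 6 of 60 post values missing (10%), adding the covariates as main effects moved the mixed-model estimate from 0.785 to 0.764, from 0.469 to 0.438, and from 1.377 to 1.368. The SEs went from 0.297 to 0.298, from 0.311 to 0.312, and from 0.304 to 0.302. The estimate shifts slightly, and precision hardly changes.

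**5. Size of the loss.** Per-dyad variance of the change score is 2σ²(1 − rho). Residual variance after regression on baseline is σ²(1 − rho²). The ratio is (1 + rho)/2, below 1 for every rho under 1. The same true effect therefore acts like d/√((1 + rho)/2), with df = 2n − 3. At 26 per arm and d = 0.8:

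| rho | Variance ratio | Effective d | Power | n per arm for 80% |
|---|---|---|---|---|
| change score | 1 | 0.800 | 80.7% | 26 |
| 0.3 | 0.65 | 0.992 | 93.9% | 17 |
| 0.5 | 0.75 | 0.924 | 90.4% | 20 |
| 0.7 | 0.85 | 0.868 | 86.6% | 22 |
| 0.8 | 0.90 | 0.843 | 84.6% | 24 |
| 0.9 | 0.95 | 0.821 | 82.7% | 25 |

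Deducting two more degrees of freedom for gender and VABS-3 lowers these powers by less than 0.1 percentage point. At d = 0.5 and 26 per arm, the change score has 42.4% power, and ANCOVA has 59.2% (rho 0.3), 53.2% (0.5), 48.3% (0.7) or 44.2% (0.9).

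**The case against.** The strongest reply is that nothing in the plan is wrong. The outcome is defined as change, the sample size is computed on change, and the model tests change. The stated 80% power is met at 26 per arm. This stands: the point is about efficiency and a nearly inert adjustment, not about bias or a faulty figure.

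A reader might infer that the covariates cannot affect the result at all, so that the trial would report as adjusted an effect that is not. The article does not support that. The cancellation is exact only for main-effect covariates with complete data. Dropout moves the estimate a little. Covariate-by-time terms are not mentioned but not excluded either, and they would change it even with complete data (0.725 to 0.696, 0.234 to 0.284 and 1.325 to 1.338 in the three sets above). How the covariates enter may be settled in an analysis plan that is not shown.

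A reader might also infer that ANCOVA is free. It costs one to three degrees of freedom, which is trivial. More importantly, baseline is assessed after randomization in mothers who know their arm. Change-score and ANCOVA analyses both assume that allocation did not affect baseline EA, and they could diverge if it did. This weakness is shared, so it does not favour the change score, but it cannot be undone for dyads already assessed.

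On the inclusion rule, it is fair to say that where the covariates are inert, selecting them cannot distort the primary estimate. Both are named in advance, and nothing says that selection will use tests on outcome data. The rule matters more once the covariates do affect the estimate, as they would under ANCOVA.

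**Conclusion.** The point holds as a recommendation to improve a valid analysis. The planned time-by-group effect is the raw difference in mean EA change. Gender and VABS-3 as main effects leave it and its SE unchanged with complete data, and add essentially no precision at 10% dropout. Adjusting for baseline EA would raise power at 26 per arm and d = 0.8 by about 2 points (rho 0.9) to 13 points (rho 0.3). The direction of the gain follows from the variance ratio for any rho below 1. Its size depends on rho and on equal pre and post SDs, neither of which the article gives. The comparison also rests on baseline EA being unaffected by allocation. The change should be made, but the trial is not invalid without it.

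**What to change.** - Prespecify as primary an ANCOVA of post-intervention EA total on group, baseline EA total, VABS-3 and child gender. A mixed model with baseline means constrained equal between arms is an acceptable equivalent; in that case, state how the covariates enter.
- Always include these covariates, and delete the reference to statistical relevance from the inclusion rule.
- Use the same form for IPS, PPS and ToP, each with its own baseline.
- Keep the group-by-time mixed model as a sensitivity analysis. This also preserves the link to the sample-size basis and to the mediation analysis, which uses change scores.
- For dyads not yet enrolled, take the baseline assessment before allocation is disclosed. Report how the two analyses compare, since a divergence could point to an effect of allocation on baseline EA.

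The analysis changes need only wording and one to three degrees of freedom, with no new data or visits. Moving baseline ahead of disclosure changes the order of procedures for the remaining dyads. The Status and timeline section reports 40 dyads recruited and 30 completed, so the wording should be fixed before any outcome data are analysed by arm.

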### Study hypotheses

Mothers and children from the JP intervention group will demonstrate greater improvements in mother-child interaction quality as measured by EA and IPS, compared to the psycho-educational parent counseling group.Mothers and children from the JP intervention group will show greater improvement in their playfulness outcome measures, compared to the psycho-educational parent counseling group.Participation in the JP dyadic intervention will contribute to an improvement in mothers’ and children’s playfulness, which consequently will mediate the increase in EA and IPS.

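### Hypothesis 3 is simple mediation, but the plan picks among four PROCESS models by a rule that reads as data-dependent; two of the four make the indirect effect conditional on a covariate

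*Protocol article*

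**What the plan says.** Under Study hypotheses, the third hypothesis is that the intervention improves mothers' and children's playfulness, "which consequently will mediate the increase in EA and IPS". No moderator appears there or under Study objectives.

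Under Data analyses, Quantitative data, the mediators are "the playfulness scores of parents and children (each score entered separately") and the outcomes are "the change scores of the primary outcome of EA total sum scores and IPS". Two mediators and two outcomes make four mediator–outcome pairs. The model for each pair is settled by "selecting model 4, 5, 7, or 14 based on the relationship between the covariates involved and the study variables". The rule for covariates is that "only covariates with both theoretical and statistical justification (e.g., child’s VABS-3 score, gender) will be incorporated into the model". For inference, the article states that "indirect effects will be estimated via bootstrap confidence intervals". The same paragraph qualifies the whole exercise: "given our modest sample size of n = 60, the proposed mediation analyses should be regarded as exploratory and interpreted with caution".

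**The concern.** The four PROCESS models do not answer one question. Model 4 estimates a single indirect effect, which is what hypothesis 3 asserts. Models 7 and 14 let a covariate moderate the first-stage or second-stage path, so the indirect effect becomes a set of values at different covariate levels, plus an index of moderated mediation.

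The selection criterion is how covariates relate to the study variables, and covariates must also have statistical justification. Those relations can be seen only in the trial's own data. If the model is chosen that way and a conditional effect or the index is then reported as mediation, the confidence interval takes no account of the selection, and the chance of a false mediation claim exceeds its nominal level. Mediation is a numbered hypothesis, and the Discussion expects the findings to inform playfulness as a mechanism of change, so a positive interval would carry weight.

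**Working it through.** **The plan's own figure.** The only number given for the mediation analysis is a requirement of 59–65 participants for three to four predictors at α = .05, power .80 and f² = .02. Using the noncentral F test of R² with λ = f²·N, f² = .02 needs 550 (three predictors) to 602 (four), while f² = .20 gives exactly 59 and 65. So the printed .02 looks like a misprint for .20. That is a separate matter: the figure sizes a regression, not an indirect effect, and nothing below depends on it.

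**What each model estimates** (X = group, M = playfulness, Y = outcome, W = moderator):

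- Model 4: M on X (slope a), Y on X and M (slope b for M). Indirect effect = a·b.
- Model 5: adds X·W to the Y equation. Indirect effect is still a·b; only the direct effect is moderated.
- Model 7: adds X·W to the M equation (a₁ for X, a₃ for X·W). Indirect effect = (a₁ + a₃W)·b; index = a₃·b.
- Model 14: adds M·W to the Y equation (b₁ for M, b₃ for M·W). Indirect effect = a·(b₁ + b₃W); index = a·b₃.

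The article counts at most four predictors (group, playfulness, VABS-3, gender). With both covariates kept, the Y equation of model 5 or 14 has 4 + 1 = 5.

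**Simulation inputs.** From the article: N = 60, 1:1 allocation (30 per arm), covariates VABS-3 and gender, bootstrap intervals. Assumed, because the article does not give them: the path sizes, a 95% level and the selection trigger. Data: M = aX + 0.3V + e and Y = bM + 0.3X + 0.3V + e, with V (VABS-3) and the errors standard normal, gender 50:50 and no moderation anywhere. There were 1,500 trials per scenario and 500 percentile-bootstrap resamples. Conditional effects were probed at the mean and ±1 SD of VABS-3, or at both genders.

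**Selection rule.** Three moderated models × two moderators = six interaction tests. If the smallest p is below .05, that model replaces model 4. Six independent tests would do this in 1 − 0.95⁶ = 26.5% of trials; the simulation gave 26.2–26.7%.

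**False-positive mediation, one mediator–outcome pair:**

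| True paths | Model 4 fixed | One model chosen by interaction test | Any model reported | Chosen model, average indirect effect only |
|---|---|---|---|---|
| a = 0, b = 0.5 | 5.1% | 12.5% | 22.8% | 5.3% |
| a = 0, b = 1 | 6.3% | 14.0% | 24.7% | 6.3% |
| a = 0.8, b = 0 | 5.7% | 11.5% | 20.0% | 6.1% |
| a = 0, b = 0 | 0.2% | 0.5% | 1.7% | 0.2% |

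The third and fourth columns count any conditional indirect effect or the index as mediation. In the first three rows the Monte Carlo standard error is about 0.6 to 1.1 points: √(0.05·0.95/1500) = 0.6 and √(0.25·0.75/1500) = 1.1.

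Reporting whichever of models 4 and 5 is positive gives 5.3–6.5% in the first three rows, so the inflation comes from models 7 and 14. A separate simulation with N = 60 and the same p < .05 trigger gave 4–5% with model 4 fixed, 11–14% with selection, 19–23% with any model reported, and under 1.5% with both paths null.

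**The case against.** The strongest reply is that the article already calls these analyses exploratory, advises caution, restricts covariates to limit overfitting and claims no confirmatory error rate for mediation. The primary EA comparison by the mixed model is untouched. This stands as a reason for lower severity. It is not a cure: the stated reason for the label is the sample size, not the open model choice.

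A second reply is that the exact trigger is something an analysis plan may fix. That would answer a silence, but the article states a selection rule, and that rule does not match its own hypothesis.

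Four stronger readings are tempting, and the document does not support them:

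- *The choice is declared to be made after seeing the data.* It is not. Data dependence is inferred from the criterion and from "only covariates with both theoretical and statistical justification"; theory is also required.
- *All three alternatives distort the indirect effect.* Model 5 does not.
- *The error rate is about 20%.* That counts a hit in any model, whereas the article speaks of selecting one.
- *Missing baseline terms bias both paths.* Group is randomised, so baseline differences in the group-to-playfulness path are chance imbalance. Only the playfulness-to-outcome path lacks that protection. The covariate list is also given as examples, so baseline terms are not excluded.

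**Conclusion.** The point holds in a limited form. The rule leaves the mediation model to what reads as a data-dependent choice, and two of the four options replace the hypothesised effect with conditional ones. Selection by interaction tests roughly doubles the false-positive rate per pair, from about 5% to about 11–14%; about 19–25% is a ceiling, not an expectation.

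These sizes rest on assumed path values, an assumed p < .05 trigger, no true moderation, exactly one non-zero path, and conditional effects or the index being read as mediation. Drop the last condition and there is almost no inflation; with both paths null every strategy stays below 5%. The rates are per pair and should not be multiplied across the four pairs, which share participants and are not independent. This is worth correcting in an exploratory analysis and does not threaten the primary result.

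**What to change.** State that hypothesis 3 is tested with PROCESS model 4 alone, for each of the four mediator–outcome pairs, with VABS-3 and gender always included as covariates and a bootstrap confidence interval for a·b at a stated level. Report models 5, 7 and 14, if at all, as exploratory moderation analyses with the moderator named, and do not count their conditional effects or index as support for hypothesis 3.

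Optionally, add baseline playfulness and the baseline value of the outcome as covariates. Both are already collected, and they help mainly against confounding of the playfulness-to-outcome path. They cost 2 degrees of freedom.

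The change is to wording only and needs no new data. The price is that any moderated mediation can be presented only as exploratory. Under Status and timeline, 40 dyads are recruited and 30 have completed, so the change should be recorded before the mediation data are examined.
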